## Abstract

**Background:**

Magnetic resonance (MR) imaging has been described as the most important medical innovation in the last 25 years. Over 80 million MR procedures are now performed each year and on average 2.3% (95% confidence interval: 2.0 to 2.5%) of all patients scheduled for MR imaging suffer from claustrophobia. Thus, prevention of MR imaging by claustrophobia is a common problem and approximately 2,000,000 MR procedures worldwide cannot be completed due to this situation. Patients with claustrophobic anxiety are more likely to be frightened and experience a feeling of confinement or being closed in during MR imaging. In these patients, conscious sedation and additional sequences (after sedation) may be necessary to complete the examinations. Further improvements in MR design appear to be essential to alleviate this situation and broaden the applicability of MR imaging. A more open scanner configuration might help reduce claustrophobic reactions while maintaining image quality and diagnostic accuracy.

**Methods/Design:**

We propose to analyze the rate of claustrophobic reactions, clinical utility, image quality, patient acceptance, and cost-effectiveness of an open MR scanner in a randomized comparison with a recently designed short-bore but closed scanner with 97% noise reduction. The primary aim of this study is thus to determine whether an open MR scanner can reduce claustrophobic reactions, thereby enabling more examinations of claustrophobic patients without incurring the safety issues associated with conscious sedation. In this manuscript we detail the methods and design of the prospective "CLAUSTRO" trial.

**Discussion:**

This randomized controlled trial will be the first direct comparison of open vertical and closed short-bore MR systems in regards to claustrophobia and image quality as well as diagnostic utility.

**Trial Registration:**

ClinicalTrials.gov: NCT00715806

## Background

Magnetic resonance (MR) imaging has been described as the most important medical innovation in the last 25 years [1]. There has been an enormous increase in the use of this modality in the clinical setting. Over 80 million MR procedures are now performed each year worldwide. For an MR scan, patients typically have to be placed in a long, narrow tube [2]. Thus, claustrophobia preventing MR imaging is a common problem. Between 1% and 15% of all patients scheduled for MR imaging suffer from claustrophobia and cannot be imaged, or they require sedation to complete the scan (mean: 2.3%; 95% confidence interval: 2.0% to 2.5%) [3]. Thus it can be estimated that worldwide approximately 2,000,000 MR procedures cannot be performed or are prematurely terminated due to claustrophobia. At an average cost of € 500 per MR imaging, this is equal to a loss of productivity of € 1 billion, which is an important financial loss for the health care system. Therefore, claustrophobia is not only a common problem that prevents many patients from benefiting from the findings obtained with MR imaging but also represents an important socioeconomic issue for the health care system.

Patients with claustrophobic anxiety are more likely to be frightened and experience a feeling of confinement or being closed in during MR imaging [4,5]. Those anxious patients have been reported to experience claustrophobia in up to 35% of all cases [6]. In these patients conscious sedation and additional sequences (after sedation) may be necessary to complete the examinations. This situation involves significant risks of adverse events [7-9] and is associated with extra costs because it reduces workflow, limits patient acceptance, and wastes valuable scanning time. Improving comfort during MR imaging (mainly reduction of noise and sensations of confinement by a fairly panoramic view) appears to be essential to avoid claustrophobic reactions [10,11]. The positive effect of noise reduction and improved patient-centered design (short and wide bore) has recently been shown in a large cohort study in over 55,000 patients using a newly designed closed MR unit (with 97% noise reduction and cylindrical CT-like appearance) with 1.5-T field and up to 45 mT/m gradient strength [3]. However, even on such recent scanners, claustrophobic patients cannot undergo MR imaging without potentially life-threatening sedation.

A more open vertical scanner configuration might be an alternative, but until recently such systems operated at rather low field strengths (0.2 T), resulting in poor image quality especially in imaging of the brain [12]. Thus, recently introduced open MR scanners with an all-around view and both high field (1.0 T) and high gradient strength (up to 26 mT/m) might be a valuable clinical alternative to further reduce claustrophobia while maintaining diagnostic image quality and diagnostic accuracy [13,14]. The more all-around view from the inside of open MR scanners is likely to reduce the incidence of claustrophobia. However, new closed MR scanners with patient-centered design (short and wide bore) and noise reduction have also been shown to greatly reduce claustrophobic reactions by a factor of up to 3 [3]. Nevertheless, no direct comparison of these two scanner types in regards to claustrophobia and image quality as well as diagnostic utility has been performed thus far. Therefore, it is unclear whether an open vertical or a closed short-bore MR design is more effective in reducing claustrophobia that prevents MR imaging. Moreover, by itself the design of open MR scanners cannot guarantee a reduction in claustrophobia or an improvement in patient outcome. The most decisive evidence for judging the efficacy of diagnostic tests comes from randomized comparisons in which the controlled design eliminates the biases of observational studies [15,16]. Randomized trials are needed to define the clinical role of such open MR scanners in patients with claustrophobic anxiety. Also no study has addressed which specific scanner design patients would prefer for imaging. Therefore, this study is designed to determine whether an open vertical or a closed short-bore MR design is more effective in alleviating claustrophobic anxiety preventing MR imaging and which further improvements might be necessary to reduce claustrophobia during MR imaging.

## Methods/Design

### Primary and secondary objectives

We propose to analyze the rate of claustrophobic reactions and clinical utility of an open MR scanner in a randomized comparison with a recently designed short-bore but closed scanner with 97% noise reduction. This trial will be the first to appraise the potential for claustrophobia reduction and clinical relevance of open MR scanners in claustrophobic patients with a clinical indication for MR imaging. Furthermore, this trial will analyze and compare the cost-effectiveness of the two MR scanners, which is important in view of the enormous annual loss of healthcare productivity due to claustrophobia during MR imaging. Also, patient preferences and image quality will be analyzed. Thus, this randomized trial may have the potential to influence both the clinical and economical utilization of MR imaging. If an open MR scanner can be shown to reduce claustrophobia in a randomized comparison it might be justified to recommend this approach for routine clinical application in certain high-risk anxiety patients or in certain imaging centers.

The primary aim of this study is thus to determine the ability of an open MR scanner to reduce claustrophobic reactions, thereby expanding the use of MRI in patients with claustrophobic anxiety. To achieve this, claustrophobic reactions (while entering the scanner room or during the MR procedure) that prevent MR imaging without sedation will be compared in the two randomized study groups. Thus, the question to be answered by this project is whether an open vertical or a short-bore MR design will alleviate claustrophobia that prevents MR imaging to a greater extent. The main secondary aims are the correlation of patients' scores in several validated psychological self-report questionnaires with the occurrence of claustrophobic events, the duration of MR imaging in the two groups, and to systematically analyze if and what further design improvements might be necessary to reduce claustrophobia during MR imaging in the future. Therefore, patient preferences concerning MR scanner design will be determined (Figure 1, Table 1). These insights are important to be able to define which further improvements by vendors might be necessary to reduce claustrophobic reactions during MR imaging.

**Figure 1 F1:**
[figure not shown]
**Drawings of four MR scanners which will be used in the custom-made questionnaire to assess which specific MR scanner design is evaluated to be the most attractive**. Patients will be asked to rank the four MR scanner types according to their preferences. First, this assessment will be done assuming equal diagnostic utility of the MR scanners, and second, assuming for scanner **A **good, for scanner **B **very good, for scanner **C **moderate and for scanner **D **adequate diagnostic utility. **Panel A **shows the open MR scanner with a vertical magnetic field design and 1-T field strength (Panorama, Philips). **Panel B **shows the closed MR scanner with a short- and wide-bore design and 1.5-T field strength (Magnetom Avanto, Siemens). **Panel C **shows an open MR scanner with a one column design and a 0.4-T vertical magnetic field. **Panel D **shows a MR scanner with a 0.6-T horizontal magnetic field and a top/front-open design which allows upright positioning of the patient, while patients have to be examined in supine position on the scanners **A-C**. This information will allow defining which further improvements by the vendors might be necessary to reduce claustrophobic reactions during MR imaging.

**Table 1 T1:** Summary of the items addressed in the custom-made questionnaire to assess satisfaction with the MR scan and preferences concerning MR scanner design

Item	Range
Preparation and information	Excellent/Good/Satisfactory/Fair/Poor
Concern	Not at all/Very little/Little/High/Very high
Comfort	Excellent/Good/Satisfactory/Fair/Poor
Feeling helpless/embarrassed	Not at all/Little/Moderate/Strong/Very strong
Anxiety	Horizontal visual analogue scale of 10 cm (0-100)
Noise	Horizontal visual analogue scale of 10 cm (0-100)
Pain	Horizontal visual analogue scale of 10 cm (0-100)
Complications	Yes/No/If yes, which complications
Reasons for premature termination (if applicable)	Free text
Reasons for successful completion (if applicable)	Free text
Willingness to undergo future examinations on the MR scanner	Yes/No/Maybe
General satisfaction with the MR scan	Excellent/Good/Satisfactory/Fair/Poor
**Summary**	
Advantages/Disadvantages of the respective MR scanner	Free text
Ranking of four MR scanners of different design assuming equal diagnostic utility (Figure 1)	1 to 4
Ranking of four MR scanners assuming different diagnostic utility (Figure 1)	1 to 4
Ranking of the two MR scanners used in the study (Figure 2)	1 to 2
Advantages/Disadvantages of the two MR scanners used in the study	Free text

Further secondary aims are the influence of MR imaging results on clinical management in the two groups, cost-effectiveness of the two scanners, image quality achieved in claustrophobic patients using the two scanners, patient acceptance and preference in regards to the diagnostic procedure in the two randomized study groups, and the development of patients' anxiety during 4 to 6 weeks and 7 months after MR imaging.

### Design

This is a randomized controlled trial of patients with reported claustrophobia during prior MR imaging or with the inability to undergo MR imaging in conventional scanners. Eligible patients will be randomly assigned to one of the following study groups. 1) The open MR scanner: imaging will be performed in a state-of-the-art scanner with a vertical magnetic field and 360° open design and 1-T field strength (Panorama, Philips, Figure 2A) [14], and 2) A state-of-the-art MR scanner (control group) without an open design but significant noise reduction of 97% (to below 99 dB(A)) and patient-centered design (short and wide bore) with 1.5-T field strength, which has already been shown to reduce claustrophobia by a factor of 3 compared with conventional MR scanners (Magnetom Avanto, Siemens, Figure 2B) [3]. The study design is shown in Figure 3.

**Figure 2 F2:**
[figure not shown]
**Drawings of the two MR scanners to which patients will be randomized in the study**. **Panel A **shows the open MR scanner with a vertical magnetic field with 1.0-T field strength (Panorama, Philips), up to 26 mT/m gradient strength, acoustic scanner noise of maximum 150 dB(A), and a 0.45 m high and 1.6 m wide patient aperture (0.7 m wide patient table). **Panel B **shows the closed MR scanner with 1.5-T field strength, up to 45 mT/m gradient strength, 97% noise reduction to below 99 dB(A), and a conical shaped wide (0.6 m) and short (1.5 m) bore resembling the gantry of a computed tomography scanner, which has been shown to reduce claustrophobia by a factor of 3 (Magnetom Avanto, Siemens).

**Figure 3 F3:**
[figure not shown]
**Chart of CLAUSTRO study design. The diagram depicts the randomization procedure, patient flow, and data analysis**. **Abbreviations: **AKV = Fragebogen zu körperbezogenen Ängsten, Kognitionen und Vermeidung [19]. BDI-II = Beck Depression Inventory II [24]. CF = Consent Form. CLQ = Claustrophobia Questionnaire [21]. FSS-III = Fear Survey Schedule III [20]. RWCCL = Revised Ways of Coping Checklist [29]. STAI = State-Trait Anxiety Inventory [18].

In order to improve patient acceptance, patients who are assigned to imaging in one MR scanner but cannot bear this procedure due to claustrophobia will not be sedated (with conscious sedation according to the standards of the American Society of Anesthesiology) [17], but will be cross-referred to imaging in the other scanner in order to preclude adverse events associated with sedation (Figure 3) [7-9]. This will also allow direct comparison of the two options in those patients as an ancillary study, which would otherwise be unethical. If patients cannot tolerate imaging in the first MR scanner in which they are assigned without claustrophobic reactions, this will be categorized as an event for the primary hypothesis of this project. In case patients cannot undergo imaging in either of the two scanners, conscious sedation according to the standards of the American Society of Anesthesiology will be performed (using Dormicum IV) to enable imaging [17].

Anxiety will be measured using different validated psychological self-report questionnaires such as the Spielberger State-Trait Anxiety Inventory [STAI] [18], the "Fragebogen zu körperbezogenen Ängsten, Kognitionen und Vermeidung [AKV]" [19], the Fear Survey Schedule [FSS-III] [20], and the Claustrophobia Questionnaire [CLQ] [21].

This randomized study has been approved by the local institutional review board at Charité. The clinical experiments will be performed according to the DECLARATION OF HELSINKI - Ethical Principles for Medical Research Involving Human Subjects and the Medizinproduktgesetz (German Medicinal Products Law).

This is an investigator-sponsored industry-independent study.

### Patients

Patients with reported claustrophobia during MR imaging or with inability to undergo MR imaging in conventional scanners because of claustrophobic anxiety will be eligible for the study and subsequent randomization if they have a clinical indication for MR imaging of the head, spine, or shoulder. Patients must not have any absolute or relative contraindication to MR imaging for safety reasons [22], must not have a body weight of more than 200 kg (maximum table weight), will be primarily examined without conscious sedation, and have to be at least 18 years old. Patients must have at least moderate levels of anxiety towards claustrophobic situations as determined using the Claustrophobia Questionnaire [CLQ] [21] (an arithmetic mean of at least 1.0 must be reached by rating anxiety on a scale from 0 to 4 for each of 26 items). All patients will have to give written informed consent before randomization.

### Sample size and statistical analysis

We expect claustrophobia rates in this high-risk patient cohort of 20% in the control group (recent closed short-bore MR imaging) and 5% in the intervention group (open MR imaging). With 82 evaluable patients per group we will achieve the desired power of 80%. Conservatively taking into account an expected drop-out rate of 5%, a total of 174 patients, 87 per group, have to be allocated.

The assumed claustrophobia rates are based on 1) all previous publications on claustrophobia during MR imaging as summarized [3], 2) an expected prevalence of claustrophobic reactions in conventional MR scanners in the study population of at least 60%, and 3) the ability of both open and the recently designed short-bore but closed MR scanners to significantly reduce claustrophobia preventing MR imaging to approximately 5 and 20%, respectively, as indicated in recent nonrandomized pilot studies [3,13,14].

The primary endpoint, claustrophobia that prevents MR imaging, will be evaluated in the intention-to-treat population using a χ^2 ^test. Secondary endpoints will be evaluated by parametric or nonparametric analysis of variance or Mantel-Haenszel tests according to scaling. Appropriate parameters of effect size (e.g., odds ratios) with confidence intervals will be calculated. Subgroups (e.g., sex, age groups, direction of scanning [head-first vs. feet-first]) will be analyzed exploratively.

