### MR imaging and image analysis

#### MR imaging

MR imaging will be performed in the supine position using phased-array coils. On the open MR scanner the following coils will be used: a large body coil for imaging of the spine, a small flex coil for imaging of the shoulder, and, to alleviate the feeling of confinement, the neck coil will be used for imaging of the head (in an upside-down position) making use of the elliptical coil design available. If the neck coil is not tolerated for head imaging on the open MR scanner, a multipurpose flex coil can be used as a second alternative. On the closed short-bore MR scanner the spine-array coils that are integrated into the table will be used for imaging of the spine, a small 1-channel circular polarized flex coil will be used for imaging of the shoulder, and a 12-channel bird-cage head coil will be used for imaging of the head. For imaging of the cervical spine, the shoulder, and the head, patients will be examined head-first on both scanners because feet-first imaging, which alleviates claustrophobia by a factor of more than 10 [3], is not possible for these diagnostic questions. For lumbar spine imaging, a feet-first approach can and thus will be utilized on both scanners. Contrast-enhanced sequences will only be obtained if clinically indicated. On the following pages the MR sequences and their characteristics are listed allowing a convenient comparison of the sequence approaches used on both MR scanners for imaging of the head, spine (cervicothoracic, and thoracolumbar), and shoulder (Tables 4, 5, 6, and 7). For detailed information on the sequence characteristics see Additional files 1, 2, 3, and 4. The primary aim of the sequence setup is to obtain a voxel size that is as similar as possible on both scanners. Differences in acquisition time might result from this aim due to different field strengths and gradients.

**Table 4 T4:** Head MR imaging sequences*

	Magnetom Avanto	Panorama

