### Follow-up after 4 to 6 weeks

At the initial follow-up, the STAI [18], AKV [19], FSS-III [20], and CLQ [21] questionnaires will be repeated. The State questionnaire of the STAI will be repeated in two versions assessing the current state of anxiety and the state of anxiety during MR imaging (if accomplished without sedation).

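### The primary chi-square is valid but leaves out scan direction, a factor known before randomisation that the article credits with a more than tenfold effect; stratifying on it is a small, nearly free gain

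*Protocol article*

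**What the plan says.** Protocol article, Sample size and statistical analysis: the primary endpoint, claustrophobia that prevents imaging, is compared by a chi-square test in the intention-to-treat population. No stratum or covariate is named. Scan direction appears only here: "Subgroups (e.g., sex, age groups, direction of scanning [head-first vs. feet-first]) will be analyzed exploratively". The planning rates are given as "We expect claustrophobia rates in this high-risk patient cohort of 20% in the control group" and "5% in the intervention group (open MR imaging".

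Same article, MR imaging: the text refers to "feet-first imaging, which alleviates claustrophobia by a factor of more than 10 [3". Lumbar spine examinations are done feet-first on both scanners. Head, shoulder and cervical spine examinations are done head-first on both. The study assistant records the anatomical region examined.

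On secondary endpoints the article gives only the family of methods: "Secondary endpoints will be evaluated by parametric or nonparametric analysis of variance or Mantel-Haenszel tests according to scaling".

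**The concern.** Direction follows from the clinical indication, which every patient must have to be eligible. It is therefore settled before randomisation, and the scanner assignment cannot change it. By the article's own figures its effect on the primary event (more than tenfold) exceeds the fourfold scanner effect the trial is powered for (20% against 5%). Such a factor is a natural stratifier for the primary test.

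Leaving it out has two costs. Variation that direction could explain stays in the comparison. And if one arm receives more low-risk feet-first patients by chance, the unstratified comparison absorbs the difference. About 82 × 0.20 + 82 × 0.05 = 20.5 events are expected, so a few misplaced events are visible. If only the unadjusted test is pre-specified, an adjustment made after an imbalance is seen will look post hoc.

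**Working it through.** **Inputs from the article.** Rates 20% and 5%; 82 evaluable and 87 allocated per group; direction factor of more than 10, taken as 10.

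**Assumed, because the article does not give them.** Two-sided alpha 0.05; feet-first share f from 10% to 50%; the factor of 10 acts equally in both arms, as a risk ratio or as an odds ratio; randomisation not stratified by direction.

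**1. The plan's own figure.** The article says "With 82 evaluable patients per group we will achieve the desired power of 80" per cent. Exact enumeration at 82 per group gives 80.5% for Fisher's exact test, 78.3% for the continuity-corrected chi-square and 85.8% for the uncorrected chi-square. The stated power is thus reproduced with Fisher's test. For dropout, 82 / 0.95 = 86.3, rounded up to 87, so 174 in total, as in "expected drop-out rate of 5%, a total of 174 patients, 87 per group, have to be allocated".

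**2. Stratum risks.** With overall risk p and a risk ratio of 10, head-first risk h = p / ((1 − f) + f/10) and feet-first risk g = h/10. For f = 30% the denominator is 0.73:
- closed scanner: h = 0.20/0.73 = 27.4%, g = 2.7%
- open scanner: h = 0.05/0.73 = 6.8%, g = 0.7%

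**3. Power at 82 per group (200,000 simulated trials per scenario).** With stratum size T, n₁ and n₂ patients per arm, m events in total and x₁ events in arm 1, the stratified statistic is [Σ(x₁ − m·n₁/T)]² / Σ[n₁n₂m(T − m) / (T²(T − 1))], referred to chi-square on 1 degree of freedom.

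| Feet-first share | Plain chi-square | Stratified, odds ratio 10 | Stratified, risk ratio 10 |
|---|---|---|---|
| 10% | 85.8% | 86.1% | 86.2% |
| 20% | 85.8–85.9% | 86.4% | 86.8% |
| 30% | 85.8–85.9% | 87.1% | 87.3% |
| 40% | 85.8% | 87.6% | 87.8% |
| 50% | 85.8–85.9% | 88.4% | 88.7% |

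The gain runs from 86.1 − 85.8 = 0.3 to 88.7 − 85.8 = 2.9 points. With both arms at 12.5%, overall type I error is 4.8–5.0% for both tests.

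**4. Type I error given an imbalance near the 95% limit** (82 per group, both arms at 12.5%, risk ratio 10, 400,000 simulated trials each). The expected spurious risk difference is (h − g) × (a − b)/82, where a and b are the feet-first counts. At f = 30%, h = 0.125/0.73 = 17.1% and g = 1.7%, so 15.4 × 12/82 = 2.3 points.

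| Share | Feet-first, arm vs arm | Plain chi-square | Stratified | Spurious difference |
|---|---|---|---|---|
| 10% | 12 vs 4 | 5.4% | 4.9% | 1.2 points |
| 20% | 21 vs 11 | 5.8% | 4.8% | 1.7 points |
| 30% | 31 vs 19 | 6.5% | 5.0% | 2.3 points |
| 40% | 39 vs 27 | 6.8% | 4.8% | 2.6 points |
| 50% | 47 vs 35 | 7.6% | 4.9% | 3.0 points |

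**5. Events in the feet-first stratum, 87 per group, both arms together.** At f = 20% (risks 2.4% and 0.6%): 17.4 × 0.030 ≈ 0.5. At f = 50% (3.6% and 0.9%): 43.5 × 0.045 ≈ 2.

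**The case against.** The plain chi-square is not an error. It holds its level overall, and its power at 82 per group already exceeds the 80% target. The gain is at most about 3 points. A spurious difference of 1.2 to 3.0 points, even near the limit of plausible imbalance, is small beside the planned 15. All of that stands, so a reader should not infer that chance imbalance is likely to overturn the result.

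The inputs are soft, and this stands too. The tenfold figure is cited from a cohort of 55,734 outpatients, not from patients selected for claustrophobia. The feet-first share is not given. The text does not describe how allocation is done, and the figure said to depict it is not shown. If randomisation is already stratified by body region or direction, the imbalance argument largely falls away, though the analysis should then still reflect that factor. Nor is the stratum perfectly defined: the text gives no direction for thoracic imaging, while the sequence tables are for cervicothoracic and thoracolumbar spine.

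Scan direction is also not ignored altogether, since it is a named subgroup. But a subgroup analysis does not adjust the primary comparison, so this answers the point only in part.

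A reader might further infer that the follow-up analysis ignores baseline anxiety scores. These questionnaires are completed at enrolment, and at 4 to 6 weeks "the STAI [18], AKV [19], FSS-III [20], and CLQ [21] questionnaires will be repeated". The article does not support that inference. Analysis of variance is named without model terms. A repeated-measures analysis with baseline as a time point would fit both that wording and the secondary aim of following anxiety over time. Model terms are also detail that a condensed article commonly leaves to the full plan. Nothing in the article supports adjusting questionnaire scores for scan direction either.

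**Conclusion.** The point holds for the primary test only, as a modest improvement to a method the article does fix. The chi-square is valid. Stratifying by direction would add about 0.3 to 3 power points, provided the tenfold ratio applies in this population and 10 to 50% of patients are scanned feet-first. If randomisation is not stratified by direction, it would also hold conditional type I error at 4.8–5.0% where the chi-square reaches 5.4–7.6% near the 95% imbalance limit (6.5% at 31 versus 19, 30% share). No conclusion follows about the analysis of follow-up questionnaire scores.

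**What to change.** Make the primary test a Cochran-Mantel-Haenszel test stratified by planned scan direction (head-first or feet-first). Set the stratum from the indication before randomisation, and state in advance which stratum thoracic examinations belong to.

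Report one pre-chosen effect measure with its confidence interval, for example the Mantel-Haenszel risk difference. That is a weighted average over strata and stays close to the planned contrast: at a 30% share, 0.7 × (27.4 − 6.8) + 0.3 × (2.7 − 0.7) = 15.0 points. A stratified odds ratio is a conditional quantity and differs from the marginal one, so the choice should not be left open. Keep the plain chi-square as a sensitivity analysis.

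The cost is wording, settled before unblinded data are seen. Body region is already recorded, and the sample size does not change. The small downside is that the feet-first stratum will hold few events (about 0.5 to 2 at shares of 20 to 50%) and adds little information of its own.
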